**PROTOCOL SYNOPSIS**

**Protocol Number:** P-01-2005

**Title:** A Phase I, Non-Randomized, Open Label, Single Dose, Dose-Escalation Safety Study of Recombinant Human Glucocerebrosidase (prGCD) in Healthy Volunteers

**Study Phase:** 1

**Study Site:** Jerusalem Phase I unit, Hadassah Medical Organization, Jerusalem, Israel

**Test Material:** human prGCD 15 units/kg; 30 units/kg; 60 units/kg and vehicle

**Dose:** human prGCD will be administered as an intravenous infusion (IV) delivered over 1.5 hour. The rate of infusion is to be 135 mL/1.5 hr (1.5ml/minute). The infusion rate will be the same over 90 minutes for all doses. All subjects will receive all doses in a sequential manner starting with vehicle. Subjects will be closely monitored for 2 hours from the time of the initiation of the infusion.

Vehicle will be given at the baseline visit. The initial human prGCD dose of 15 units/kg will be given at Day 8; 30 units/kg dose will be administered on Day 15, and 60 units/kg dose on Day 22.

**Route of Administration:** Intravenous (IV)

**Controls:** Each subject will receive vehicle and thereby will be his/hers own control.

**Objectives:**

**Primary**

To evaluate the safety of three escalating doses of human Glucocerebrosidase (prGCD) intravenously administered once a week in healthy volunteers.

**Secondary**

To evaluate the pharmacokinetic profile of prGCD after IV administration in healthy volunteers

**Design:** This is a phase I, non-randomized, open label, safety study of three escalating single doses of human prGCD administered as an intravenous infusion (IV) in healthy volunteers.

Eligible subjects will receive the vehicle on Day 1 followed by human prGCD on Day 8 (15 units/kg), Day 15 (30 units/kg), and Day 22 (60 units/kg). At each visit, blood samples for clinical chemistries and CBC with a differential count, will be collected prior to dosing and at 24h post the initiation of the infusion. Blood samples for PK analysis will be collected at 0, 5, 45, 80, and 90 minutes during the infusion and 100, 115, 130, 150, 180, 210 minutes, and 24 hours post-infusion. Subjects will be discharged from the clinic after 8 hr on the day of the infusion and will arrive again 24 hr from the initiation time of infusion for blood draw and additional safety assessment.. A follow-up visit will occur on Day 29.

**Blinding:** Open-label study

**Sample Size:** A total of 6 healthy volunteers will participate

**Method of Subject Assignment:** Open label

**Primary Outcome Measures:** Safety as measured by adverse events, changes in vital signs, physical examination and laboratory test results.

**Secondary Outcome Measures:**

- Pharmacokinetic parameters
- Immunological profile including: IgE, anti human prGCD antibodies, eosinophils and proteinuria

**Plan for Obtaining Adverse Events:** All volunteered, elicited and observed adverse events (AEs) will be documented.

**Plan for Data Analyses:** Safety parameters, as well as changes from baseline, will be examined and summarized for descriptive purposes. Safety will also be assessed through the recording of adverse events. Adverse events will be classified by body system using the MedDRA classification, and tabulated based on the incidence, severity, and causality to study treatment.

TABLE OF CONTENTS

[LIST OF ABBREVIATIONS 9](#__RefHeading___Toc102708696)

[1. INTRODUCTION 10](#__RefHeading___Toc102708697)

[1.1. Rationale 10](#__RefHeading___Toc102708698)

[1.2. Summary of non clinical and clinical studies 10](#__RefHeading___Toc102708699)

[2. OBJECTIVES 11](#__RefHeading___Toc102708700)

[2.1. Primary 11](#__RefHeading___Toc102708701)

[2.2. Secondary 11](#__RefHeading___Toc102708702)

[3. STUDY DESIGN 11](#__RefHeading___Toc102708703)

[3.1. Indication 12](#__RefHeading___Toc102708704)

[3.2. Blinding 12](#__RefHeading___Toc102708705)

[3.3. Controls 12](#__RefHeading___Toc102708706)

[3.4. Randomization 12](#__RefHeading___Toc102708707)

[3.5. Dose Rationale 12](#__RefHeading___Toc102708708)

[3.6. Stopping Criteria 13](#__RefHeading___Toc102708709)

[3.7. Study Flow Chart 13](#__RefHeading___Toc102708710)

[4. SUBJECT POPULATION 13](#__RefHeading___Toc102708711)

[4.1. Inclusion Criteria 13](#__RefHeading___Toc102708712)

[4.2. Exclusion Criteria 13](#__RefHeading___Toc102708713)

[5. STUDY PROCEDURES AND VISIT SCHEDULE 14](#__RefHeading___Toc102708714)

[5.1. Pre-Screening Visit (Day -1) 14](#__RefHeading___Toc102708715)

[5.2. Screening Visit (Day 0) 14](#__RefHeading___Toc102708716)

[5.3. Baseline Visit (Visit 1, Day 1, Treatment visit) Baseline Visit can be done ± 1 day from planned visit. 14](#__RefHeading___Toc102708717)

[5.4. Visits 2-2a, 3-3a and 4-4a (Treatment Visits, Day 8-9, Day 15-16, and Day 22-23), visit 2,3 and 4 can be done ± 1 day from planned visit. 15](#__RefHeading___Toc102708718)

[5.5. Visit 5 (Follow-up Visit, Day 29) 16](#__RefHeading___Toc102708719)

[5.6. Observations and Measurements 16](#__RefHeading___Toc102708720)

[5.6.1. Blood Tests. 16](#__RefHeading___Toc102708721)

[5.6.2. PK Analysis 16](#__RefHeading___Toc102708722)

[11.3. Case Report Forms and Study Records 28](#__RefHeading___Toc102708762)

[11.4. Record Retention 28](#__RefHeading___Toc102708763)

[11.5. Protocol Deviations 28](#__RefHeading___Toc102708764)

[12. Quality control and quality assurance 28](#__RefHeading___Toc102708765)

[13. Study protocol agreement form 29](#__RefHeading___Toc102708766)

[14. PUBLICATION 29](#__RefHeading___Toc102708767)

[15. REFERENCES 30](#__RefHeading___Toc102708768)

[16. APPENDIX 1: Study flow chart 31](#__RefHeading___Toc102708769)

[17. APPENDIX 2: Common Toxicity Criteria 32](#__RefHeading___Toc102708770)

LIST OF ABBREVIATIONS

| AE | Adverse Event |
| --- | --- |
| ANF | Anti Nuclear Factor |
| AST | Aspartate Aminotransferase |
| AUC | Area Under the Curve |
| CBC | Complete Blood Cell including differential count of white blood cells |
| cGMP | Current Good Manufacturing Practice |
| CHO | Chinese Hamster Ovary |
| CPK | Creatine Phosphokinase |
| CRF | Case Report Form |
| CTC | Common Toxicity Criteria |
| ECG | Electrocardiogram |
| ER | Endoplasmic Reticulum |
| ERC | Ethical Review Committee |
| ERT | Enzyme Replacement Therapy |
| FDA | Federal Drug Administration |
| GCP | Good Clinical Practice |
| GlcCer | Glucocerebroside (Glucosylceramide) |
| GLP | Good Laboratory Practice |
| HBsAg | Hepatitis B Surface Antigen |
| HCV | Hepatitis C Virus |
| HIV | Human Immunodeficiency Virus |
| ICH | International Conference on Harmonization |
| IgE | Immunoglobulin E |
| IRB | Institutional Review Board |
| IV | Intravenous |
| LDH | Lactate Dehydrogenase |
| MedDRA | Medical Dictionary of Regulatory Activities |
| MOH | Ministry of Health (Israel) |
| NDA | New Drug Application |
| PI | Principal Investigator |
| PK | Pharmacokinetics |
| pNP-Glc | para-Nitrophenyl-beta-D-Glucopyranoside |
| prGCD | Plant Cell Expressed Recombinant Human Glucocerebrosidase |
| PT | Prothrombin Time |
| PTT | Partial Thromboplastin Time |
| SAE | Serious Adverse Event |
| WFI | Water For Injection |

# INTRODUCTION

Gaucher disease, the most prevalent lysosomal storage disorder, is caused by mutations in the human glucocerebrosidase gene (GCD) leading to reduced activity of the lysosomal enzyme glucocerebrosidase and thereby to the accumulation of substrate glucocerebroside (GlcCer) in the cells of the monocyte-macrophage system. This accumulation leads to the visceral manifestations of hepatosplenomegaly, anemia and thrombocytopenia, as well as to the skeletal features and less frequently also to lung involvement.

The identification of GCD deficiency as the etiology of Gaucher disease stimulated the development of enzyme replacement therapy (ERT) as a therapeutic strategy for this disorder, which has been proven as safe and effective over the past 14 years, in over 3000 patients using either natural or recombinant purified human glucocerebrosidase derived from mammalian tissue culture production systems. Studies have shown that glycosylation plays a crucial role in glucocerebrosidase activity and uptake to target cells, and indeed, in the formulations currently used special steps of deglycosylation are required in order to generate exposed mannose residues as the terminal glycoside side chains (Bijsterbosch MK. et al. 1996; Friedman B. et al. 1999; Furbish FS. et al. 1981; Doebber T. et al. 1982).

Several approaches are currently being utilized to control and tailor protein glycosylation in plants, including specific targeting to subcellular compartments and the genetic modification of glycosylation machinery. As mention above, when human glucocerebrosidase is produced in mammalian cell culture, the glycosylation must be remodeled in order to generate an active form of the enzyme. Therefore the expression of human glucocerebrosidase in plants cells resulting in high mannose structures during production in the plant tissue culture system is of great value.

## Rationale

Human glucocerebrosidase has been used successfully for the clinical treatment of Gaucher disease for several years from both natural and recombinant sources (CHO production platform). This is the first trial to utilize a recombinant active form of lysosomal enzyme, glucocerebrosidase, (human prGCD) which is expressed and purified in a bioreactor system from transformed carrot plant root cell line.

Since the glycosylation pattern of recombinant human glucocerebrosidase must possess high mannose structures to increase uptake in target cells, the expression of human glucocerebrosidase in plant cells could be of great value. As mentioned above several approaches are utilized to control and tailor protein glycosylation in plants (Dwek RA *et al*. 2002). Protalix’s approach attempts to localize the expression to a specific compartment in the cell. For example, retaining the protein in the endoplasmic reticulum (ER) prevents plant specific modification from being carried out in the Golgi (Neuhaus JM and Rogers JC 1998; Vitale A and Galili G 2001). This approach has been adopted in developing active human prGCD.

## Summary of non clinical and clinical studies

Two GLP toxicology studies where performed and completed with the current human prGCD recombinant protein, derived from plant tissue culture bioreactor system. The first was a study in rodents, performed at Harlan Biotech Israel, In this study a single dose of: Vehicle; 1X; 5X; 10X of the clinical dose (60units/kg) were given to 24 mice. A 14-day observation period included clinical signs, body weight, detailed necropsy and gross pathological examination. In this study no obvious treatment related adverse reactions, no gross pathological findings, and no mortality were observed.

The second study was a 28 days repeat dose in non-human primates (Marmosets) preformed at Huntingdon Life Sciences Laboratory UK. Twenty-four (24) animals (4/sex/group/dose) were intravenously infused daily with 1X or 5X of the clinical dose (60units/kg) adjusted to animal body surface area The 1X clinical dose, 60U/kg, is equivalent to 1.8 mg/kg in humans which corresponds to 66 mg/m2 (using the standard human surface area conversion factor of 37). The dose of 66mg/m2 corresponds to 11 mg/kg in marmosets (using the conversion factor of 6 for marmoset monkeys). Therefore, 5 times the clinical dose is 55mg/kg in Marmoset monkeys.

In-life data were collected and analyzed. Preliminary results indicated no obvious treatment related adverse reactions, no gross pathological findings, and no mortality. Ophthalmoscopy and electrocardiography indicated no findings related to the treatment. In addition, all blood and urine tests were found to be within normal ranges for Marmosets. More detailed description of the above toxicology study can be found in the pre-clinical section in the Investigator’s Brochure.

# OBJECTIVES

## Primary

To evaluate the safety of administration of three escalating single intravenous doses of human glucocerebrosidase (prGCD) in healthy volunteers

## Secondary

To determine the pharmacokinetic profile of human prGCD after IV administration in healthy volunteers

# STUDY DESIGN

The proposed investigation will be a phase I, single-center, non-randomized, open label, safety study of three single escalating doses of human prGCD administered as an intravenous infusion (IV) to six healthy volunteers. Subjects meeting the entry criteria will be eligible to receive study drug. Urine will be collected 24 hours prior to screening to assess renal function. Seven visits are scheduled for this study: pre-screening (Day -1), Screening (Day 0), baseline (Day 1), Visit 1 (Day 8), Visit 2 (Day 15), Visit 3 (Day 22) and follow-up visit (Day 29). The study procedures for each visit are presented in the study flow chart (Appendix 1). The duration of study is 29 days.

Subjects will be monitored over 24 hours from the commencement of the infusion of each dose at the Hadassah medical center, Phase I unit. The treatment will consist of a single dose infused for 1.5 hours (1.5mL/min). The infusion rate may be adjusted according to subject symptoms and signs: slower rate (1mL/min) upon adverse effect or faster (2mL/min.) upon lack of any symptom and signs. The vital signs for each subject will be monitored during infusion. ECG will be done at baseline and at 8 hours following the infusion. Subjects will remain at the clinic for 8 hours post-infusion and will be discharged if no AEs are observed. Subjects will return to the clinic 24h post initiation of infusion for additional safety assessment. Vital signs will be recorded during the infusion and PK sampling every 30 minutes (up to 3.5 hrs), and afterward at 8 and 24hrs post infusion.

Each subject will receive a single IV dose of vehicle at the baseline visit (Day 1). Blood samples for PK will be collected prior to dosing (0) and at 5, 45, 80 and 90 minutes during the infusion and 100, 115, 130, 150, 180, 210 minutes and 24 hours from initiation of infusion. On Day 8, subjects will receive a single 15 units/kg of study drug and will have the same blood samples taken as per Day 1. On Day 15, subjects will receive a single 30 units/kg of study drug and have the blood samples taken as per Day 1. On Day 22, subjects will be administered a single dose of study drug of 60 units/kg, and have the same procedures performed as Day 1.

The Principle Investigator will review all test results and AE report 24h prior to escalation to the next dose level. The dose will be increased based on review of drug toxicity by the Principle Investigator and the Medical Director of Protalix Ltd. A follow up safety visit will take place at Day 29.

Plasma levels of human prGCD will provide a pharmacokinetic profile, including AUC0-inf, Tmax, Cmax and Cmin and will be calculated for each subject.

All PK samples of human prGCD will be analyzed at the end of the study for all subjects. This data will be used as adjunct information for a safety review, which will include a review of adverse events, changes in vital signs, physical examination and clinical laboratory test results. Unexpectedly high plasma concentrations will be reviewed for correlation to related adverse events.

This study is conducted according to FDA and European GCP guidelines.

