## Baseline Visit (Visit 1-1a, Day 1-2, Treatment visit) Baseline Visit can be done ± 1 day from planned visit.

1. Baseline data will be collected at time 0 immediately prior to infusion of study medication and at 24h (baseline a) from initiation of infusion.
2. Body weight, vital signs and physical examination.
3. Concomitant medications
4. Electrocardiogram (ECG) (will be performed only at time 0 and 8hr post infusion.)
5. Withdrawal of 22 mL venous blood for laboratory tests, pre infusion (time 0) and 24h post infusion which include:
   1. Serum chemistries including electrolytes (K, Na, Cl, HCO3, Ca, and P), liver function tests (AST, ALT, LDH, AlkP, GGT, and Bilirubin), Renal function tests (BUN, and Creatinine,) CPK, Serum proteins(albumin and globulin), Cholesterol, and Uric Acid
   2. Complete blood cell count (CBC), and coagulation profile (PT, PTT)
   3. ANF, ESR, C3 (C3 test should be done both at time 0 and 24hr post infusion)
6. Urinalysis
7. 5mL PK blood for plasma sample prior to dosing
8. Prepare drug (vehicle) for infusion (see Section 6.5)
9. Administer the investigational drug (see Section 6.2) and monitor safety as described below:

| Parameters | Pre-infusion | During and Post-infusion |
| --- | --- | --- |
| Temperature | + | +a |
| Blood Pressure | + | +a |
| Pulse Rate | + | +a |
| Respiratory Rate | + | +a |

a Vital signs will be measured prior to infusion and every 30 minutes during infusion and at 8, 24 hours post infusion

1. Withdrawal of 5 ml blood for plasma samples at 0,80, 210 minutes and 24 hours post-infusion.
2. Withdrawal of 5ml blood for serum for antibody detection and characterization at 24h post infusion
3. Adverse events

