4. ANF, ESR ,C3
5. Eosinophils, IgE
6. Urinalysis
7. Withdrawal 5ml PK blood for plasma sample prior to dosing
8. Administer the investigational drug (see Section 6.2) and monitor the same safety parameters as described in Visit 1
9. Withdrawal of 5ml blood for plasma samples at 0, 5, 45, 80 and 90 min during infusion and 100, 115, 130, 150, 180, 210 minutes and 24 hours post-infusion.
10. Withdrawal of 5ml blood for serum for antibody detection and characterization at 24h post infusion
11. Adverse events
12. Serum prGCD protein level will be checked at the end of the study for all subjects.
13. Anti human prGCD antibodies will be analyzed at the end of the study for all patients from blood serum samples taken 24hr post each infusion.

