## Study Drug Administration

Human prGCD will be administered as an intravenous infusion (IV) delivered over 1.5 hours. The rate of infusion is to be 135 mL/1.5 hrs (1.5ml/minute). The infusion rate will be the same over 90 minutes for all doses. The infusion rate may be adjusted according to subject symptoms and signs: slower rate (1mL/min) upon adverse effect or faster (2mL/min.) upon lack of any symptom and signs. Subjects will be monitored for 24 hours from the commencement of the infusion of each dose at the Hadassah medical center, Phase I unit.

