# APPENDIX 1: Study flow chart

|  | Pre-Screening | Screening | Visit 1-  (Baseline) | Visit 1a-  (Baseline a) | Visit 2 | Visit 2a | Visit 3 | Visit 3a | Visit 4 | Visit 4a | Follow-up visit |
| --- | --- | --- | --- | --- | --- | --- | --- | --- | --- | --- | --- |
| Day | -1 | 0 | 1 | 2 | 8 | 9 | 15 | 16 | 22 | 23 | 29 |
| Informed consent |  | x |  |  |  |  |  |  |  |  |  |
| Inclusion/exclusion criteria |  | x |  |  |  |  |  |  |  |  |  |
| Demographics |  | x |  |  |  |  |  |  |  |  |  |
| Medical history & current medications |  | x |  |  |  |  |  |  |  |  |  |
| Concomitant medications |  | x | x |  | x |  | x |  | x |  | x |
| Vital Signs |  | x | xb | x | xb | x | xb | x | xb | x | x |
| Temperature |  | x | x |  | x |  | x |  | x |  | x |
| Body Weight |  | x | x |  | x |  | x |  | x |  | x |
| Physical Examination |  | xd | x |  | x |  | x |  | x |  | x |
| Chest X-ray |  | xc |  |  |  |  |  |  |  |  |  |
| IV infusion |  |  | x |  | x |  | x |  | x |  |  |
| AE Assessments |  |  | x | x | x | x | x | x | x | x | x |
| ECG |  | x | x |  | x |  | x |  | x |  |  |
| Laboratory tests |  |  |  |  |  |  |  |  |  |  |  |
| Serum chemistriese |  | x | x | x | x | x | x | x | x | x | x |
| CBC PT, PTT, C3, ESR, ANFe |  | x | x | x | x | x | x | x | x | x | x |
| Urinalysis at 0 and 24 hours post infusion | xg | x | x | x | x | x | x | x | x | x | x |
| plasma prGCD protein level (PK)f |  |  | x | x | x | x | x | x | x | x | x |
| Eosinophils, IgE |  | x | x | x | x | x | x | x | x | x | x |
| Serum pregnancy test |  | x |  |  |  |  |  |  |  |  | x |
| Anti human prGCD antibodies in serum |  |  |  | x |  | x |  | x |  | x | x |
| HBsAg, HCV and HIV |  | x |  |  |  |  |  |  |  |  |  |

a Visit which is scheduled 24 h post each infusion visit

b Vital signs (temperature, blood pressure, pulse rate, respiratory rate and cardiac rhythm) will be measured prior to infusion and every 30 minutes during infusion and at 8 and 24 hours post infusion

c If not obtained within the past 6 months prior to study start and available for reading by the PI

d Including height

e Withdraw 22 ml whole blood pre infusion (time 0) and 24h post infusion

f Withdrawal of 7 ml blood at, 0 and at 5, 45,80 and 90 minutes during the infusion and 100, 115, 130, 150, 180, 210 minutes and 24 hours from infusion initiation

g Urine collection 24 hours prior to screening visit to assess renal function

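### Section 3 takes vital signs every 30 minutes up to 3.5 h, but the visit procedures and flow chart stop them when the infusion ends and resume only at 8 h

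*Protocol*

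**What the plan says.** The protocol gives the timing of vital signs in three places.

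- **Section 3, Study Design:** "Vital signs will be recorded during the infusion and PK sampling every 30 minutes (up to 3.5 hrs), and afterward at 8 and 24hrs". The 3.5 h limit equals 210 minutes, the last same-day PK time in that section, which is counted from the start of infusion.
- **Section 5.3, Baseline Visit, footnote a:** "Vital signs will be measured prior to infusion and every 30 minutes during infusion and at 8, 24 hours post infusion".
- **Appendix 1, footnote b:** vital signs "will be measured prior to infusion and every 30 minutes during infusion and at 8 and 24 hours post infusion".

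Section 5.4, for the 15, 30 and 60 units/kg visits, sets no timing of its own beyond monitoring during infusion. It tells staff to "monitor the same safety parameters as described in Visit 1", so the Section 5.3 footnote governs every prGCD infusion. Section 3 also sends the reader to the chart: "The study procedures for each visit are presented in the study flow chart (Appendix 1").

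The synopsis defines the primary outcome as "Safety as measured by adverse events, changes in vital signs, physical examination and laboratory test results". Section 9.2 lists vital signs and infusion-related toxicity among the safety parameters.

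**The concern.** Section 3 requires half-hourly readings for about two hours after the infusion ends. The two places that staff and CRF designers are most likely to work from do not contain them. There is no order of precedence, and Section 3 itself points to the flow chart for the procedures at each visit.

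Vital-sign change is part of the primary outcome. Section 1.1 describes this as the first trial of the enzyme produced in a carrot root cell line, and the same six volunteers receive doubling doses a week apart. If the shorter schedule is followed, a symptom-free change in blood pressure, pulse, temperature or respiratory rate shortly after the infusion leaves no record. The PK samples from 100 to 210 minutes would also have no vital signs beside them, although Section 3 plans to use PK as an adjunct to a safety review that includes vital-sign changes.

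**Working it through.** The protocol states no figure of its own here. The check sets the schedules side by side and counts the readings.

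**Inputs.** Volume 135 mL at 1.5 mL/min (Section 6.2), so 135 / 1.5 = 90 minutes. Six subjects (synopsis). Four infusions each: vehicle and three prGCD doses (Section 6.1.1). The 3.5 h limit is taken from the start of infusion, as Section 3 does for its PK times. The Section 3 sentence does not name a pre-dose reading. It is counted in both schedules and does not affect the difference.

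| Time from start of infusion | Section 3 | Section 5.3 and Appendix 1 |
| --- | --- | --- |
| Pre-dose | 1 | 1 |
| 30, 60, 90 min | 3 | 3 |
| 120, 150, 180, 210 min | 4 | 0 |
| 8 h and 24 h | 2 | 2 |
| Total per infusion | 10 | 6 |

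**Size over the study.**
- Infusions: 6 × 4 = 24, of which 6 × 3 = 18 are prGCD.
- Sets of readings: 24 × 10 = 240 against 24 × 6 = 144.
- In dispute: 240 − 144 = 96, which is 96 / 240 = 40% of the Section 3 total.
- After prGCD: 18 × 4 = 72. After vehicle: 6 × 4 = 24.

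**Time from the end of infusion to the next reading.**
- Section 3: 120 − 90 = 30 minutes.
- Section 5.3 and Appendix 1: 8 h if the 8 h runs from the end of infusion, or 8 − 1.5 = 6.5 h if it runs from the start. The text does not settle this. Section 5.3 places the next-day assessment 24 h from initiation in one item and 24 h post infusion in another, for the same visit.

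**Does another part of the text reconcile them?** The Section 5.3 table has a column covering the period during and after infusion, but its footnote limits the post-infusion readings to 8 and 24 h. PK blood is drawn at 210 minutes at every infusion visit, vehicle included (Sections 5.3 and 5.4), so the Section 3 limit is workable at all four visits. No clause gives one section priority.

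**The case against.** The strongest reply is that the footnotes omit readings but do not forbid them. Section 3 contains every reading that the other two places require, so a site that follows Section 3 complies with all three. The trial has one centre and six subjects, so centres cannot differ. Subjects stay in the clinic for 8 h, symptomatic events would be seen, and the stopping rule does not depend on these readings. All of this stands and limits the weight of the point. It does not remove the point, because a site that follows the flow chart, as Section 3 directs, has no cue to take the extra readings.

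A reader might also infer more than the documents support:

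- **A third schedule in the synopsis.** The sentence "Subjects will be closely monitored for 2 hours from the time of the initiation of the infusion" does not mention vital signs, and Sections 3 and 6.2 separately provide 24 h monitoring. It is not a competing vital-sign schedule. Nor can a firm limit be derived for when a slowed infusion would outlast that window, because Section 6.5 raises the volume to 150 mL for subjects over 90 kg at 60 units/kg.
- **A lost comparison with vehicle.** Section 9.2 compares end-of-study parameters with baseline, and Sections 9.4.2 and 9.4.4 make the analysis descriptive. No time-matched comparison of each dose with vehicle is planned.
- **A compromised escalation decision.** Section 3 bases escalation on test results, the AE report and drug toxicity. It names vital-sign changes only for the later review that uses the PK data. That escalation would suffer is inference.
- **A certain 8 h gap.** It may be 6.5 h.

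**Conclusion.** The conflict is in the current text and nothing resolves it. At the planned rate, 4 sets of vital signs per infusion, 96 in all and 72 after prGCD, are required by Section 3 and absent from the visit procedures and the flow chart. If the shorter schedule is used, the next reading comes 6.5 to 8 h after the infusion ends, instead of 30 minutes. Symptom-free changes in a named primary safety outcome would then be missed at each dose level.

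The count assumes that all 24 infusions are given as 135 mL at 1.5 mL/min. The permitted adjustments ("slower rate (1mL/min) upon adverse effect or faster (2mL/min.) upon lack of any symptom and signs") would move some readings into or out of the infusion. At 150 mL and 1.5 mL/min the infusion lasts 150 / 1.5 = 100 minutes, and the disputed readings are still four.

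This is more than clerical, because it decides whether primary-outcome data are collected just after each infusion. It should be corrected, but it does not undermine the design or the stopping rule.

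**What to change.** Bring Section 5.3 footnote a and Appendix 1 footnote b into line with Section 3. Suggested wording for both: *Measure vital signs before dosing, every 30 minutes through the infusion and same-day PK sampling (to 3.5 h from the start of infusion), and at 8 and 24 hours.* Section 5.4 then inherits the change. Add the 120, 150, 180 and 210 minute time points to the CRF for all four infusion visits. This wording leaves open whether the 8 h runs from the start or the end of infusion, which the documents do not settle.

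The cost is two footnote edits, four CRF time points per infusion visit and, compared with the shorter schedule, four more sets of readings per infusion (96 in all). They fall while subjects are already in the clinic, so no extra visit, blood or subject is needed. The downside is that more readings in six volunteers will give more isolated out-of-range values to describe.

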## Visits 2-2a, 3-3a and 4-4a (Treatment Visits, Day 8-9, Day 15-16, and Day 22-23), visit 2, 3 and 4 can be done ± 1 day from planned visit.

1. Baseline data will be collected at time 0 immediately prior to infusion of study medication and at 24h from initiation of infusion.
2. Body weight, vital sign (will be monitored during infusion) and physical examination.
3. Concomitant medications
4. Electrocardiogram (ECG) (will be performed only at time points 0 and 8 hr.)
5. Prepare drug for infusion (Section 6.5)

- Infuse 15units/kg (Visit 2)
- Infuse 30 units /kg (Visit 3)
- Infuse 60units/kg (Visit 4)

1. Concomitant medication use
2. Withdrawal of 22 mL venous blood for laboratory tests, pre infusion (time 0) and 24h post infusion which include:
3. Serum chemistries including electrolytes (K, Na, Cl, HCO3, Ca, and P), liver function tests (AST, ALT, LDH, AlkP, GGT, and Bilirubin), Renal function tests (BUN, and Creatinine,) CPK, Serum proteins(Albumin,Globulin), Cholesterol, and Uric Acid Complete blood cell count (CBC), and coagulation profile (PT, PTT)

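### The escalation review falls before the day-7 safety laboratory set is drawn, and nothing requires that set to be read before the dose is doubled

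*Protocol*

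**What the plan says.** Section 3 (Study Design) sets the time of the review: "The Principle Investigator will review all test results and AE report 24h prior to escalation to the next dose level". The next sentence gives the basis for escalating, "The dose will be increased based on review of drug toxicity", and assigns that review to the investigator and the sponsor's Medical Director. It names no laboratory set and no time limit.

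The sampling times are the same in three places:

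- Synopsis, Design: "clinical chemistries and CBC with a differential count, will be collected prior to dosing and at 24h post the initiation of the infusion".
- Section 5.4 (Visits 2 to 4): "Baseline data will be collected at time 0 immediately prior to infusion of study medication and at 24h from initiation of infusion", and for the safety bloods "Withdrawal of 22 mL venous blood for laboratory tests, pre infusion (time 0) and 24h post infusion which include".
- Appendix 1, footnote e: "Withdraw 22 ml whole blood pre infusion (time 0) and 24h post infusion". The flow chart gives urinalysis, eosinophils and IgE the same two visits per dose.

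Doses of 15, 30 and 60 units/kg are planned for Days 8, 15 and 22, each with a window of one day either way. The flow chart has no visit between a 24 h visit and the next dosing visit. Section 5.4 lists the pre-infusion draw and the infusion but does not make the infusion wait for the results.

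**The concern.** A review held a day before dosing cannot include a sample taken just before dosing. The pre-infusion set on Days 15 and 22 is also the only laboratory look at the preceding dose after 24 h and before the next one. A change in liver enzymes, creatinine, eosinophils or urine protein that causes no symptoms, is absent at 24 h and has appeared by about day 7 would be in that sample. A site following the text exactly could draw it and double the dose with the result unread.

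The protocol itself treats day 7 as worth measuring: after the last dose it schedules a full laboratory set on Day 29, seven days later. Laboratory results are part of the primary outcome, and the secondary outcomes include "Immunological profile including: IgE, anti human prGCD antibodies, eosinophils and proteinuria". Section 1.1 introduces the plant-cell product with "This is the first trial to utilize a recombinant active form of lysosomal enzyme", so caution between dose steps is in keeping with the protocol's stated reason for escalating in stages (Section 3.5).

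The stopping rule in Section 3.6 does not fill the gap. It needs a serious event that threatens life and is judged certainly due to the drug, and it has no laboratory criterion.

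**Working it through.** The protocol gives no figure to reproduce here; the check is the order of events. Visit numbers follow Section 5.4.

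**Inputs.** Dose days 8, 15 and 22 (Synopsis). Laboratory sets at time 0 and 24 h (Section 5.4, Appendix 1). Review 24 h before the next dose (Section 3). Visit window ±1 day (Section 5.4). Six subjects (Synopsis).

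**Nominal schedule**

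| Step (units/kg) | Dose escalated from | Its 24 h set | Review | Next time-0 set |
| --- | --- | --- | --- | --- |
| 15 to 30 | Day 8 | Day 9 | 15 − 1 = Day 14 | Day 15 |
| 30 to 60 | Day 15 | Day 16 | 22 − 1 = Day 21 | Day 22 |

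- Age of the newest set at the review: 14 − 9 = 5 days; 21 − 16 = 5 days.
- Age of that set at the next infusion: 15 − 9 = 6 days; 22 − 16 = 6 days.
- Time from the preceding dose to the time-0 set: 15 − 8 = 7 days; 22 − 15 = 7 days.

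**With the windows (first step; the second gives the same values).** Visit 2 can fall on Days 7 to 9, so its 24 h visit falls on Days 8 to 10. Visit 3 can fall on Days 14 to 16, so the review falls on Days 13 to 15.

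- Age at the review: 13 − 10 = 3 to 15 − 8 = 7 days.
- Age at the next infusion: 14 − 10 = 4 to 16 − 8 = 8 days.
- Preceding dose to time-0 set: 14 − 9 = 5 to 16 − 7 = 9 days.

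The windows move the dates but not the order: the 24 h set comes before the review, and the time-0 set after it.

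**Other readings of the 24 h wording.** If it means at least 24 h before dosing, or a review of the 24 h results, the time-0 set is still outside it.

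**Count, within each subject's own schedule.** Sets drawn after the first active dose and before the last: Day 9, Day 15 time 0, Day 16, Day 22 time 0, so 4 × 6 = 24. The Day 14 review can use Day 9 (6 sets). The Day 21 review adds Day 15 time 0 and Day 16 (12 sets). Sets that can reach a review: 6 + 12 = 18. Sets that reach none for the same subject: the 6 from Day 22 time 0.

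**The case against.** The strongest reply is that this is an omission and not an instruction. The sentence basing the dose increase on toxicity has no time limit, and Section 8 lets the investigator withdraw a subject in that subject's interest. Nothing stops a careful investigator from reading the time-0 result and holding the dose. That is right: the protocol permits dosing with the result unread but does not direct it. The withdrawal rule, and the rule in Section 7 that counts clinically significant laboratory changes as adverse events, nevertheless work only on a result that someone has read.

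The second reply is that the expected risk is low. Section 3.5 reports earlier safe use of 30 and 60 units/kg, the two steps at issue, with other enzyme preparations. Section 1.2 reports marmosets infused daily for 28 days at one and five times the clinical dose, scaled for body surface area, with blood and urine tests in the normal range. Both points stand and lower the priority. One might discount the marmoset tests as preliminary, but that word opens an earlier sentence about reactions, gross pathology and deaths. It does not clearly attach to the blood and urine results.

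Three stronger readings are tempting and not supported:

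- **No late effect can be seen before 60 units/kg.** The Day 15 time-0 set can reach the Day 21 review, so a delayed effect of 15 units/kg can be seen in time.
- **The Day 22 time-0 results inform no review at all.** This holds only within a subject. The protocol does not say that all six are dosed on the same calendar day, so an earlier subject's result could inform a later subject's review.
- **Primary endpoint data are lost.** Section 9.2 compares safety parameters at study end with baseline, and every set is still drawn and available for analysis. The issue is only when a result is read.

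The deferral of PK and antibody analysis to the end of the study is a separate choice and is not challenged here.

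**Conclusion.** The point holds in a limited form. For each doubling, the review has one of the two laboratory sets drawn after the dose being escalated from and before the next dose. The missing one is the day-7 set, and no text requires it to be read before infusion. The step to 60 units/kg matters most, because the Day 22 time-0 set is the only day-7 view of 30 units/kg before the highest dose.

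The exposure is confined to a symptomless laboratory change that is absent at 24 h and present near day 7. Adverse events, vital signs, ECG and the 24 h results can all still hold a dose. The conclusion rests on the nominal visit days, with the ranges shown for the windows, and on counting within each subject's own schedule. It is a minor to moderate matter, worth amending because the samples are already being taken.

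**What to change.** Amend Sections 3 and 5.4:

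1. On Days 15 and 22, take the existing pre-infusion blood and urine on arrival. Start the infusion only after the investigator has read that day's chemistry, CBC with differential (including eosinophils) and urinalysis and has confirmed the step for that subject.
2. Refer any clinically significant new abnormality to the Medical Director before dosing.
3. For tests not available the same day (C3, IgE, ANF and, if applicable, PT/PTT and ESR), use the latest available value. The gap stays open for these.
4. State that the review 24 h before dosing covers adverse events, vital signs, ECG and the safety laboratory results then available, and not the deferred PK and antibody results.

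**Cost.** Waiting on 2 × 6 = 12 subject-days. The protocol gives no laboratory turnaround. Assuming 1 to 4 h, the total is 12 × 1 = 12 to 12 × 4 = 48 subject-hours. The clinic day, already a 1.5 h infusion followed by 8 h of observation, becomes longer by the same 1 to 4 h. The safety sample is then taken some hours before the infusion and no longer immediately before it, so the definition of time 0 in Section 5.4 needs a matching change. No extra samples or visits are needed if results come back the same day; the site should confirm this before the amendment is written.
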